## Abstract

**Introduction::**

Chronic neck pain is a common musculoskeletal disorder that is associated with functional disability and decreased of quality of life. Electrophysical agents are commonly used to relieve pain, however the effects of combined use of these agents are little studied. The objective is to investigate the efficacy of photobiomodulation and electrical stimulation to relieve pain, both in isolation and combined.

**Materials and methods::**

This a 4-arm randomized placebo-controlled trial with patient and evaluator blinded. This study will be performed in Department of Physical Therapy at Federal University of São Carlos, São Carlos/SP, Brazil. One hundred and forty-four patients with chronic neck pain will be randomized into 4 groups: active photobiomodulation therapy with active electrical stimulation, active photobiomodulation therapy, active electrical stimulation, or placebo treatment. They will receive 10 sessions of treatment. Primary outcome: pain intensity (measured by pain numerical rating scale) posttreatment. Secondary outcomes: pain during movement, neck disability, range of motion, pressure pain threshold, temporal summation, conditioned pain modulation, depressive symptoms, pain catastrophizing, quality of life, analgesic intake, and global perceived effect at posttreatment (10 sessions). Pain intensity and global perceived effect will also be measured after 6 weeks randomization.

**Discussion::**

The findings of this study might clarify the importance of using the photobiomodulation therapy and transcutaneous electrical nerve stimulation for patients with chronic neck pain.

**Trial registration::**

NCT04020861. https://clinicaltrials.gov/ct2/show/NCT04020861?term=NCT04020861&draw=2&rank=1.

## Introduction

1

Chronic neck pain is defined as pain or discomfort in the posterior cervical region between the superior nuchal line and the first thoracic spinous process and/or shoulder girdle with or without pain referred to the upper back or arms and continuing for at least 3 months.^[1–3]^ Neck pain is considered non-specific when it is not related to any specific pathology such as inflammatory rheumatic disease, osteoporosis, cancer, or radiculopathy.^[2]^

Neck pain has an incidence of 10.4% to 21.3% and a prevalence of 17.1% to 73%^[1]^ and it is increasing with population aging.^[4,5]^ It is estimated that 71% of the population will experience neck pain some time in their lives with women being more likely than men to experience it.^[1,4]^ According to Global Burden of Disease, in 2015, more than a third of a billion people had neck pain of >3 months duration and neck pain was ranked the fourth leading cause of disability-adjusted life years (DALYs) globally just after ischemic heart disease, cerebrovascular disease, and lower respiratory infection.^[5,6]^ With such a large population affected by this problem, increasing knowledge about effective treatments for it should be considered a global health priority.

Photobiomodulation therapy (PBMT) and analgesic electrical currents are non-pharmacologic resources used in the treatment of patients with neck pain.^[4,7–9]^ PBMT is light therapy that uses lasers (light amplification by stimulated emission of radiation) or LED's (light emitting diodes) from the visible to the infrared spectrum, a portion of the spectrum where light interacts with chromophores leading to photophysical and photochemical reactions in tissues.^[10]^ Low-level laser therapy is nonthermal and it may have a stimulating effect on target tissues.^[11]^ Therefore, it is used in several musculoskeletal conditions to decrease pain and inflammation as well as stimulate collagen metabolism and wound healing.^[11]^ Côté et al,^[8]^ in their clinical practice guidelines, recommend the use of PBMT in combination with patient education for the treatment of chronic neck pain and associated disorders. This recommendation was based on 6 randomized clinical trials (RCTs)^[9,12–16]^ in which PBMT was better than placebo treatment and, in the majority of studies, the neck pain was associated with myofascial pain syndrome.^[8]^ Having been established as an effective treatment, it is then important to verify whether PBMT is superior to other analgesic agents including electrical currents.

Normally, electrical currents are applied through adhesive electrodes over the skin surface. This method is known as transcutaneous electrical nerve stimulation (TENS).^[17,18]^ Typically, TENS units deliver pulsed electrical currents with either balanced asymmetrical or symmetrical biphasic rectangular waveforms in which frequency, pulse duration, and amplitude can be adjusted.^[17,18]^ It is widely used in both acute and chronic painful conditions.^[17–19]^ Some studies have hinted that TENS might be more effective than placebo or as effective as other interventions for patients with neck pain.^[4,7,20–24]^ Unfortunately, the evidence is of low quality, the studies are heterogeneous, and more trials should be performed with larger patients samples, higher quality, and attention to adequate principles of application and evaluation of TENS.^[25]^

Both therapies, PBMT and TENS, are commonly used in clinical practice for patients with neck pain. The use of these electrophysical agents is important to decrease pain and may have the added benefits of decreasing the use of painkillers and facilitating exercise during therapy. However, the literature is still controversial, the studies are heterogeneous and of low quality and most of them only investigated pain and functional impairment. Therefore, more high-quality trials are required to verify the efficacy of these agents and the best methods of applying them. In addition, until this moment, no studies were found that investigated the combined effect of PMBT and TENS. These electrophysical agents have different ways of producing analgesia so we hypothesize that combined treatment with PMBT and TENS may have a synergistic action and result in a decrease in pain faster and/or for a longer time. Therefore, the objective of this study is to verify the efficacy of PBMT and TENS, isolated or combined, in relation to pain, functional disability, range of motion, pressure pain threshold, temporal summation, conditioned pain modulation, depressive symptoms, pain catastrophizing, quality of life, analgesic intake, and global perceived effect in patients with non-specific chronic neck pain.

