### Intervention

2.7

The patients will receive 10 consecutive days of treatment, with the exception of weekends. Each session will last around 1 hour, and it will be conducted by the same therapist during the same period of the day. After the initial evaluation, the patients will be randomly allocated to one of 4 groups: PBM + TENS group, PBM group, TENS group, and Placebo group. In the PBM + TENS group (n = 36) the patients will undergo the active PBMT and active TENS, in the PBM group (n = 36) the patients will be undergo the active PBMT and placebo TENS, in the TENS group (n = 36) the patients will undergo the placebo PBMT and active TENS, and in the Placebo group (n = 36) the patients will undergo the placebo PBMT and placebo TENS.

The equipment Antares (Indústria Brasileira de Equipamentos Médicos - IBRAMED, Amparo, São Paulo, Brazil) will be used for active and placebo photobiomodulation therapy (PBMT). Table 1 shows the parameters that will be used in the active PBMT.^[26]^ The patient will be prone. If laying prone is not possible, they will be seated. The treatment area will be defined as the painful area. A simulation of laser application will be performed for the placebo PBMT. The cluster probe will be positioned on the painful area for the same duration as active PBMT, the equipment will be turned on and set, but the trigger will be not activated, and no beam will be applied.

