### Sample size

2.22

The sample size of the study was performed based on the pain intensity outcome (as measured by the pain numerical rating scale) with mean difference of 2.3 points and an estimated standard deviation of 2.76 points.^[13]^ Statistical power of 80% was considered with an alpha of 5% and possible sample loss of up to 15%. Accordingly, a total of 144 patients will be required for the study. The sample calculation was performed using the Minitab software, version 17, (Minitab, Inc., PA).

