## Discussion

3

This randomized controlled trial will investigate the effect of isolated and combined of photobiomodulation and electrical stimulation for chronic neck pain patients.

It will be possible to determine whether the application of one agent is superior to the other and/or whether the application of both is superior to isolated application of one of them, as well as whether they are superior to placebo treatment.

It will be possible to verify the efficacy of these agents not only in relation to intensity of pain but also in relation to range of motion, pressure pain threshold, central sensitization, functional disability, pain catastrophizing, depressive symptoms, and quality of life.

It has a high-quality design that leads to strong clinical evidence. The findings of this study might clarify the importance of using the PBMT and TENS for patients with chronic neck pain.

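### The article hypothesises synergy between PBMT and TENS, but the comparisons it names and its sample size are differences between two arms, which alone cannot support synergy

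*Protocol article*

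**What the plan says.** The Introduction presents the combination as the unstudied question and states: "we hypothesize that combined treatment with PMBT and TENS may have a synergistic action". It expects this to show as quicker or more lasting pain relief. The formal objective that follows is broader and does not mention synergy: "the objective of this study is to verify the efficacy of PBMT and TENS, isolated or combined, in relation to pain" and the other outcomes.

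Intervention (2.7) crosses active or placebo PBMT with active or placebo TENS, 36 patients per arm. In the TENS group, for example, "the patients will undergo the placebo PBMT and active TENS". Every patient receives both procedures, real or sham, and all four cells of the 2x2 are filled.

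The Discussion names the questions the trial can answer. First, "It will be possible to determine whether the application of one agent is superior to the other"; then "whether the application of both is superior to isolated application of one of them"; then "as well as whether they are superior to placebo treatment". Sample size (2.22) is calculated on pain intensity "with mean difference of 2.3 points and an estimated standard deviation of 2.76 points", with 80% power, 5% alpha and up to 15% loss, giving 144. Statistical analysis (2.23) names a parametric or nonparametric test, chosen after a normality check, and no contrast. The article does not mention an interaction or a factorial analysis, and does not define synergy as a contrast between arms.

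**The concern.** In the usual statistical sense, synergy means that the combination relieves more pain than the two separate effects added together. That is a contrast across all four arms. Each comparison in the Discussion uses two arms, and so does the single mean difference behind the sample size. A combination that beats PBMT alone and TENS alone shows that the second agent adds something. It does not show that the sum is exceeded.

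The combined effect is the novel part of this trial. If only the named comparisons are carried out, the stated hypothesis stays unanswered, and a positive result on them can be read as synergy when the effects are additive or less. The reader would also not learn how imprecise the answer on synergy is at this sample size.

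**Working it through.** **Inputs.** SD 2.76, difference 2.3, loss 15%, total 144 (Sample size, 2.22); 36 per arm (Intervention, 2.7). Evaluable per arm: 36 × 0.85 = 30.6, taken as 31. Two-sided 5% is assumed, as sidedness is not stated. The effect of each agent over placebo is my assumption: the article does not say which comparison the 2.3 refers to.

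**The plan's own figure.** For one two-arm comparison, n = 2 × (1.96 + 0.84)² × 2.76² / 2.3² ≈ 23 per arm. Dividing by 0.85 gives 28 per arm, 112 in total (116 with the t-distribution). The stated 144 is not reproduced from these inputs alone. That is a separate matter, and nothing below depends on it. At 31 per arm, a 2.3-point difference between two arms has about 90% power.

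**The synergy contrast.** In points of relief: I = (both) − (PBM) − (TENS) + (placebo). Its variance is 4 × SD²/n, against 2 × SD²/n for a two-arm difference.

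- SE at 31 per arm: 2.76 × √(4/31) = 0.99. The 95% half-width is 1.98 × 0.99 = 1.96 points.
- SE at 36 per arm: 2.76 × √(4/36) = 0.92. The half-width is 1.82 points.
- Power for I = 2.3: 63% at 31 per arm, 70% at 36.
- Power for I = 1.15: 21% at 31 per arm, 24% at 36.
- Interaction detectable with 80% power at 31 per arm: about 2.8 points.
- For 80% power at I = 2.3: 46 evaluable per arm; 46/0.85 rounds up to 55, so 220 in total.

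These figures have no baseline adjustment. The correlation between baseline and post-treatment pain is not given. Assuming 0.3, 0.5 or 0.7, power for I = 2.3 becomes about 68%, 76% or 90%.

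**How often the combination beats both single agents.** Simulated normal data, 31 per arm, SD 2.76, pooled variance, unadjusted two-sided 5%, 40,000 trials per row. Relief is over placebo.

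| PBM | TENS | Both | I | Combination beats both | Interaction test signals synergy |
|---|---|---|---|---|---|
| 2.3 | 2.3 | 4.6 | 0 | 84% | 2.6% |
| 1.5 | 1.5 | 3.0 | 0 | 40% | 2.5% |
| 2.3 | 2.3 | 4.1 | −0.5 | 58% | 0.7% |
| 2.3 | 2.3 | 3.45 | −1.15 | 21% | 0.1% |
| 0 | 0 | 2.3 | +2.3 | 84% | 63% |

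Separate two-sample t-tests give 83% for the first row (20,000 trials). The first and last rows make the point: exact additivity and a 2.3-point synergy give the same chance of beating both single agents, because the combination is 2.3 points ahead of each in both cases. Only the four-arm contrast separates them.

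**The case against.** The strongest reply is that the article gets nothing wrong here and merely leaves a model to an analysis plan that is not shown. The Discussion says what the design makes possible and does not limit the analysis to that list. The formal objective is efficacy, alone or combined, and a sample size on one mean difference fits it. The synergy sentence is hedged, and it describes the consequence as faster or longer-lasting relief rather than a larger drop at the end of treatment.

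Much of this stands as a limit on the point. A reader might infer that the interaction has been ruled out, or that the investigators will report a win over each single agent as synergy. The documents support neither: an analysis plan could contain the interaction, and the Discussion speaks of superiority. Nor can a product term on post-treatment pain be the only test of the hypothesis. The 6-week pain score bears on the longer-lasting part, and the article names no pain-intensity assessment between baseline and the end of the ten sessions that would show faster relief.

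The 83% also depends on a favourable assumption. It needs 2.3 points from each agent, while the article itself calls the TENS evidence low in quality; at 1.5 points it is about 40%. The simulation ignores the bounds of the 0–10 scale. Patients may enter with a score of 3, and such patients cannot gain 4.6 points.

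What the reply does not remove is the mismatch in the text: a synergy hypothesis, a design able to address it, and named comparisons and sizing that do not. Relief that is faster or longer than with either agent alone can also arise from additive effects, so the gloss does not settle what synergy means.

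**Conclusion.** The point holds as a mismatch between the stated hypothesis and the stated comparisons and sizing. Superiority of the combination over each single agent cannot on its own support synergy. Under exact additivity it occurs in about 83% of trials at an assumed 2.3 points per agent and about 40% at 1.5. Under a half-point shortfall from additivity, with 2.3 points per agent, it still occurs in about 58%.

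The trial can estimate the interaction, but only to about ±2 points, with about 63% power for 2.3 points after 15% loss. Synergy is therefore estimated, not powered. These figures assume SD 2.76 in every arm, approximately normal scores and no baseline adjustment. The point should be dealt with before analysis, but it does not threaten the pairwise efficacy questions.

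**What to change.** In Statistical analysis (2.23):

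- Fit one linear model to post-treatment NRS with PBMT (active or placebo), TENS (active or placebo) and their product. Fit the same model to the 6-week NRS for the longer-lasting part of the hypothesis.
- Report the product term with its 95% CI as the test of greater-than-additive pain reduction at each time point. Read the pairwise differences from the same model.
- State that 144 patients give a CI of about ±2 points, and that a floor on the 0–10 scale can push the interaction towards sub-additivity.
- Where the combination only beats the single agents, claim added benefit and not synergy.

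Alternatively, reword the hypothesis in the Introduction to superiority of the combination over each agent alone, which the named comparisons do address.

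Either route changes wording and at most adds one model term. It needs no new patients or data. The price of the first is openly stated low precision for the synergy claim.

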## Materials and methods

2

### Ethical aspects and study design

2.1

This protocol study was written following the recommendations of Standard Protocol Items: Recommendations for Interventions Trials (SPIRIT) and this 4-arm randomized placebo-controlled superiority trial with patient and evaluator blinded to the allocation group will follow the guidelines recommended by Consolidated Standards of Reporting Trials (CONSORT). Figure 1 provides a flowchart of the study.

**Figure 1 F1:**
[figure not shown]
Flowchart of the study.

The study has been approved by the Human Research Ethics Committee of the Federal University of São Carlos (UFSCar; CAAE: 81711417.0.0000.5504), São Paulo, on March 2018. The protocol of this study has been registered on Clinicaltrials.gov (NCT04020861). All the patients included in the study will validate their participation by signing an informed consent form that will be explained by evaluator.

### Study setting

2.2

Patients will be recruited through the internet, posters, and radio dissemination. The study will be performed in Department of Physical Therapy of Federal University of São Carlos, Brazil, from January, 2020 until July 2019.

### Eligibility criteria

2.3

The study evaluator will verify whether the patients will be eligible to participate in the study based on patient history and clinical examination.

### Inclusion criteria

2.4

Patients with non-specific chronic neck pain, defined as pain or discomfort in the posterior cervical region between the superior nuchal line and the first thoracic spinous process and/or shoulder girdle;Neck pain for at least 3 months;Neck disability index (NDI) score of 5 points or higher;Numeric rating scale (NRS) score of ≥3 for pain intensity;Aged between 18 and 65 years;Men and women.

### Exclusion criteria

2.5

Neck pain associated with nerve root compromise (measured by clinical examination of dermatomes, myotomes, and reflexes);Previous spinal surgery;Patients treated with physical therapy for neck pain within 3 months prior to the study;Severe spinal disorders such as fractures, tumors, inflammatory, and infectious diseases;Any contraindication to low-level laser therapy or transcutaneous electrical nerve stimulation;Rheumatic, metabolic, neurological, or cardiopulmonary diseases;Patients who require artificial cardiac pacemakers;Patients with sensory deficits;Skin diseases, mainly at the current application site;History of tumors or cancer in the last 5 years;Pregnancy;Having started any physical activity in the last 2 weeks.

### Procedures

2.6

Patients will work with 2 separate researchers, 1 serving as the evaluator and the other serving as a therapist. Both are physiotherapists. The patients will be evaluated before the treatment, after the treatment (10 sessions) and 6 weeks after randomization. On the first session, the evaluator will collect sociodemographic data, medical history, and data related to the study outcomes. Then, the therapist will give each patient 10 consecutive days of treatment, with the exception of weekends, after which they will be re-evaluated by the evaluator. After 6 weeks randomization the evaluator will be in contact by telephone to the patients for a follow-up evaluation. All data entry will be coded and double-entered into an Excel spreadsheet for analysis.

### Intervention

2.7

The patients will receive 10 consecutive days of treatment, with the exception of weekends. Each session will last around 1 hour, and it will be conducted by the same therapist during the same period of the day. After the initial evaluation, the patients will be randomly allocated to one of 4 groups: PBM + TENS group, PBM group, TENS group, and Placebo group. In the PBM + TENS group (n = 36) the patients will undergo the active PBMT and active TENS, in the PBM group (n = 36) the patients will be undergo the active PBMT and placebo TENS, in the TENS group (n = 36) the patients will undergo the placebo PBMT and active TENS, and in the Placebo group (n = 36) the patients will undergo the placebo PBMT and placebo TENS.

The equipment Antares (Indústria Brasileira de Equipamentos Médicos - IBRAMED, Amparo, São Paulo, Brazil) will be used for active and placebo photobiomodulation therapy (PBMT). Table 1 shows the parameters that will be used in the active PBMT.^[26]^ The patient will be prone. If laying prone is not possible, they will be seated. The treatment area will be defined as the painful area. A simulation of laser application will be performed for the placebo PBMT. The cluster probe will be positioned on the painful area for the same duration as active PBMT, the equipment will be turned on and set, but the trigger will be not activated, and no beam will be applied.

**Table 1 T1:**
[figure not shown]
Parameters for PBMT.

The Neurodyn Portable TENS unit (Indústria Brasileira de Equipamentos Médicos - IBRAMED, Amparo, São Paulo, Brazil), which has a balanced asymmetric biphasic pulsed current, will be used for active transcutaneous electrical nerve stimulation (TENS). The patient will be prone. If laying prone is not possible, they will be seated. Two or four standard square self-adhesive electrodes (5 × 5 cm^2^) (ValuTrode, Axelgaard, CA) will be positioned around the painful area as reported by patient. The following parameters will be used: frequency of 100 Hz, phase duration of 125 μs, 30 minutes of current stimulation, and the pulse amplitude will be increased until the patient reports a strong but comfortable paresthesia (including motor level stimulation but no pain). The amplitude will be adjusted (if necessary) every 5 minutes to keep a strong but comfortable paresthesia. For placebo TENS, the device will be customized to deliver a current for 30 seconds (both channels) and then ramp off over the next 15 seconds so that it will be active only for a total of 45 seconds. This will permit the patient to feel the TENS sensation while applying the settings. The unit will also display an active indicator light suggesting to the patient that the unit is actively emitting current even after the 45 seconds. In a study comparing this placebo-TENS approach to standard placebo-TENS methods and active TENS, this transient placebo-TENS was found to improve blinding of evaluators without providing analgesia.^[27]^ Patients will be instructed to report when they feel the stimulation and every 5 minutes the patients will be asked if they are feeling comfortable.

